## Abstract

**Background:**

Caregivers may play a fundamental role in the clinical pathway of cancer patients. They provide emotional, informational, and functional support as well as practical assistance, and they might help mediate the interaction and communication with the oncologists when care options are discussed, or decisions are made. Little is known about the impact of dyadic dynamics on patient-doctor communication, patient's satisfaction, or adherence to the therapies. This study protocol aims to evaluate the efficacy of a psychological support intervention on patients-caregivers relationship and their alignment in the treatment decision-making (TDM) process and estimate related improvement in patient' compliance/adherence to treatments.

**Methods:**

A total of 102 patients-caregivers' dyads will be involved, among breast and prostate cancer patients. The study entails a pre- post- evaluation through psychological questionnaires, with a randomization of participants in two conditions, the experimental one in which subjects participate in a psychological support consultation, and the control one, where dyads do not receive any intervention. A follow up after 6 months from the enrollment is planned.

**Discussion:**

A positive impact of the psychological support intervention on patients' anxiety, depression, distress, and perceived social support is expected. Such improvements can directly affect patients' satisfaction and adherence to treatments. Data gathered from this study may inform health care providers, policy makers, and public health managers about the importance of caregiver's involvement in the cancer care pathway, and the best way to manage it. A further *impact* is to develop a specific intervention protocol to support caregivers' involvement in cancer care pathway, improve patient's wellbeing, the interaction with physicians and the compliance with the cancer treatment.

## Introduction

Caregivers' involvement in the patients' cancer care path and in the decision-making process has become more frequent in the last decades and has been recognized by a growing empirical literature, according to which most patients and caregivers preferred a collaborative or supportive caregivers' involvement (Laidsaar-Powell et al., 2017). Throughout the treatment process, from diagnostic assessment onwards, oncological patients commonly face the dramatic experience of cancer with at least one caregiver at their side, deal with visits and treatment appointments, therapies' side effects, change in daily life, experiencing significant distress (Laidsaar-Powell et al., 2017; Laryionava et al., 2018; Fatigante et al., 2021). Caregivers generally belong to the family system, often they are the spouse/partner or the adult child of the patients, in rare cases even friends can play this role (Laidsaar-Powell et al., 2017), They provide emotional, informational, and functional support as well as practical assistance, also mediating the interaction and communication with the oncologists when care options are discussed, or decisions are made (Hobbs et al., 2015; Litzelman, 2019; Schulman-Green et al., 2020; Fatigante et al., 2021).

Laidsaar-Powell et al. (2017) developed a conceptual framework (TRIO) according to which caregivers are involved in various ways in the decision-making process, concerning primarily the daily management of cancer treatments' effect. Patients almost always involve caregivers in the decision-making process, transforming the classic patient-physician interaction into a triadic relationship (patient, caregiver, and physician) (Mitnick et al., 2010; Renzi et al., 2016; LeBlanc et al., 2018). Nevertheless, patients and caregivers may have different perspectives regarding treatment decisions, experiencing episodes of conflicts or tensions between them, especially in the advanced cancer and the end-of-life context (Levine and Zuckerman, 1999, 2000; Vivian, 2006; Kramer et al., 2010; Hauke et al., 2011; Boelk and Kramer, 2012; Shin et al., 2016; Longacre et al., 2018; Benson et al., 2019; Hansen and Tjørnhøj-Thomsen, 2020). Such disagreements may have a negative impact on the patient, affecting the understanding of medical information, compliance with therapies and, consequently, the patient's quality of life, including the relationship with the caregiver (Shin et al., 2016). Poor disease-related communication between cancer patients and caregivers could increase the levels of psychological distress for both parties, making the course of treatment more complex (Speice et al., 2000). Instead, when patients and their caregivers are in line with the decisions to be made and their preferences are met, the process of care is enhanced for all the parties involved (Speice et al., 2000; Joosten et al., 2008). Moreover, caregivers' involvement in the oncological examinations was associated with both increased patients' satisfaction with respect to the care process and improved understanding of cancer-related information (Joosten et al., 2008; DuBenske et al., 2010a,b). More broadly, Krieger (2014) suggests the importance of an alignment among patient-caregiver preferences for the extent of caregiver involvement in the decision-making process.

The issue of caregivers' involvement in the therapeutic path has been also conceptualized within the ethical and bioethical literature. Within this literature, caregivers' involvement has been discussed in relation to the concept of autonomy. While some authors promoted an interpretation of autonomy as self-determination (Beauchamp and Childress, 2019), thus suggesting that the caregivers have only a supportive role (Mitnick et al., 2010), the vast majority of contemporary contributions on the topic tend nowadays to endorse the concept of “relational autonomy” (Gómez-Vírseda et al., 2020). According to the latter, people are not solipsistic agents but are defined by their relationships and depend on “significant others” to make decisions. This way, caregivers might often influence a patient's decision-making process regarding medical treatments, bringing with them a range of emotional reactions, interpersonal dynamics, and expectations (Hobbs et al., 2015; Laidsaar-Powell et al., 2016; Shin et al., 2016; Longacre et al., 2018).

Regardless the evidence about the effects that patient-caregiver interaction may have at both a psychological and decision-making levels, few studies assessed the effectiveness of psychosocial interventions, aimed at helping caregivers to be more involved in the treatment decision-making (TDM) process (Garvelink et al., 2016). Other studies focused on the effectiveness of dyadic psychological intervention on distress management (e.g., anxiety, depression, hopelessness, etc.) and patients' Quality of Life improvement (Regan et al., 2012; Griffin et al., 2014; Hu et al., 2019). The contents of psychological intervention protocols were psychoeducational, skills training or therapeutic counseling (e.g., anxiety, depression, hopelessness, etc.). These interventions could be either couple-based interventions involving both the patient and the caregiver in the same session, or interventions offered to the caregiver only, or to the caregiver and the patient independently in separate sessions (Hu et al., 2019).

Drawing upon this background, this study protocol aims to firstly evaluate the efficacy of a dyadic psychological support consultation for newly diagnosed breast and prostate cancer patients-caregivers on their level of agreement related to TDM, through a randomized research design. We also want to estimate related improvement in patient' compliance/adherence to treatments, together with the satisfaction with the (shared) medical decisions, and their psychological distress. We focus on breast and prostate cancer patients not only for a pragmatic reason, being the two most common disease in women and men, respectively, but even because they can have an early detection, so that we can explore caregivers' involvement from the diagnosis onward (Northouse et al., 2007; Dorros et al., 2010; Segrin and Badger, 2010; Oliveri et al., 2020b). Moreover, breast and prostate cancers belong to those types of cancers where caregivers' involvement can be necessary, since some decisions for therapies also involve the sphere of intimacy and fertility (Northouse et al., 2007; Dorros et al., 2010). In these cases, partners ideally play a fundamental role in making decisions, insofar as the decision has an impact on them as well (Segrin and Badger, 2010; Muzzatti et al., 2020; Cincidda et al., 2022). For this reason, the promotion of specific interventions to support dyads facing the diagnosis of breast or prostate cancer becomes even more crucial.

Accordingly, this study presents the following interrelated hypotheses:

a) The psychological support consultation will be effective in increasing the alignment between newly diagnosed breast and prostate cancer patients and their caregivers, regarding treatment decisions and in reducing or managing the possible disagreement/conflict that may arise among them.b) The psychological support consultation will improve newly diagnosed breast and prostate cancer patients' treatment adherence, satisfaction with TDM and their psychological distress.

## Methods and analysis

### Study aims

The *primary aim* of the present study is to assess whether a psychological support intervention for newly diagnosed breast and prostate cancer patients-caregivers' dyads may promote their synergy in the TDM process and may improve the compliance/adherence to treatment and the satisfaction with the (shared) medical decisions through a randomized study.

The *secondary aim* are: (a) to assess the preferences and degree of agreement between newly diagnosed breast and prostate cancer patient and caregiver on the latter's involvement in the TDM process; (b) to investigate which factors and dynamics contribute to a collaborative relationship between newly diagnosed breast and prostate cancer patient and caregiver, and determine the level of involvement of the caregiver; (c) to understand what are the effects that the involvement of caregivers have on newly diagnosed breast and prostate cancer patients in terms of patients' perceived social support, satisfaction with the clinical path, compliance with therapy, quality of life, anxiety and depression, and perceived empathic relation with clinicians.

Finally, since the issue of caregiver's involvement has been also investigated within the bioethical literature and presents bioethical connotations as well, the ethical issues surrounding this dyadic relationship will be also explored. Accordingly, in parallel with the main study, a secondary investigation exploring the presence and nature of ethical disagreements within family relationships, in the context of diagnosis of and treatment to cancer will be carried out.

### Study design and setting

This study will be conducted at the European Institute of Oncology of Milan (Italy). The IEO is a specialized Hospital and internationally recognized Cancer Center located in Italy working on research, prevention, diagnosis, and treatment of cancer. The IEO offers to the patients innovative and personalized care, from the diagnosis onward. Study design is longitudinal randomized, with a 1:1 allocation ration analyzing the proposed primary and secondary aims.

Participants will be randomly assigned to one of the two following arms: (1) dyads receiving a psychological support consultation (experimental group); (2) dyads receiving no psychological support consultation (control group). For ethical reasons, the dyads in the control group will be offered the option to receive the psychological support consultation at the end of the study, but only in case the psychological support consultation turns out to be beneficial for the dyads. Indeed, the study did not foresee a cross sectional design.

The dyads assigned to the experimental group will be contacted by the clinical psychologist to schedule an appointment for the psychological support consultation. The consultation will be performed within the period of diagnostic assessment, preferably within the date of pre-hospitalization for surgery or for starting other cancer treatments. The consultation will be carried out by a clinical psychologist with a master's degree in clinical psychology, a state certificate exam, and previous internship in psychological support intervention for cancer patients.

The consultation will last 60 min and will include the following steps and areas of focus:

- the psychologist will open the consultation by asking the dyads if they would like to narrate their emotional reaction to the cancer diagnosis, if they were together when they got the bad news or if the patients later communicated diagnosis to the caregivers. This way, the psychologist can start sharing their emotional state of the dyads and their communication style;- then, the psychologist will assess the dyad's preferences about their mutual involvement in the clinical assessment path (e.g., participating together in medical examinations) and in the decision-making process, and their level of agreement regarding the ideal care path. The psychologist can help dyads to explicit their emotional status, have an effective and assertive exchange of ideas, provide different input on how to handle the upcoming star of treatments. Moreover, the psychologist will evaluate their feelings and perception about the relationship with the medical team to assess whether a therapeutic alliance between patients, caregivers and clinicians can be structured.- finally, the psychologist will help them in reporting their emotions/fears and mutual needs, to help the dyad go through this difficult moment of life together providing adequate support to each other. During the consultation, the psychologist will be available to address even more topics of interest to the dyad to favor the care path and a better quality of life, such as how to behave with minor children or with extended family.

The psychologist who is going to carry out the consultations will be supervised by a coordinator with a specialization in psychotherapy, with the aim of solving any doubts.

The evaluation through a set of standardized questionnaire swill be carried out at three time points: initial evaluation before randomization (baseline, pre-consultation; T0), after the pre-hospitalization (and post psychological consultation for the experimental group; T1), at 6 months after the beginning of the medical treatment (T2). Between the baseline evaluation (T0) and the second evaluation (T1), the experimental group will meet the psychologist for the consultation and the control group will not receive any intervention, but both groups will have made decision about cancer treatments with their referring oncologists. The average time between the two assessment T0 and T1 is about 4 weeks (see Figure 1 for the study flowchart).

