**Figure 1 F1:**
[figure not shown]
Study protocol flowchart.

The assignment to one of the two arms will not be disclosed to the participants and to the experimenters who will interface with the subjects for consultation and psychological assessment through questionnaires. Only personnel who analyze the data collected from the study will be aware of participants who receive psychological support consultation. Participants will be randomized during T0 assessment, immediately after the collection of socio-demographic and clinical data and psychological measures.

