### Data analyses

Missing data: presence of missing data will be checked before conducting the main analyses. If a subject does not complete T1 and T2 he/she will be excluded from the analysis.

Normal distribution of continuous variables will be assessed (using skewness and kurtosis) before conducting the main analyses. Non-normal distribution will be handled by applying either non-parametric tests or SEM with an estimator for non-normal distribution.

Statistical analyses will be performed in SPSS version 25. Socio-demographic data collected in this study will be described in terms of mean, standard deviation, median, minimum, and maximum or reported frequencies in combination with confidence intervals. The preliminary analysis will be carried out through the Pearson or Spearman correlations r between the variables considered and by exploratory analysis of variance. To compare the two experimental and control groups, the *t*-tests (in case of normal distribution) or Mann-Whitney U tests (in case of non-existence of a normal distribution) will be applied, or cross tables with the chi-squared tests and (if necessary) the generalized exact Fisher's tests.

The main analysis will consist of an evaluation at different time-points of the psychometric scales, using linear models with mixed effects for repeated measures. The scales of interest will constitute the dependent variable, whereas the independent fixed factors will be the time of visit, the intervention group, the scale measured at baseline and the interaction term between the time of the visit and the intervention and, as a random effect, the patient. Multiple linear regressions will be calculated for both groups to evaluate the weight of each variable on the main outcome.

The semi-structured interviews will be analyzed by NVivo v10, a qualitative data analysis software.

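### T1 carries a post-consultation condition in the experimental arm only; with the completer exclusion, dyads that never attend can be lost from that arm alone

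*Protocol article*

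**What the plan says.** All of this is in the Protocol article.

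- **Order of events (Study design and setting).** "Participants will be randomized during T0 assessment, immediately after the collection of socio-demographic and clinical data and psychological measures". Scheduling comes after allocation: "The dyads assigned to the experimental group will be contacted by the clinical psychologist to schedule an appointment for the psychological support consultation". The session should take place "preferably within the date of pre-hospitalization for surgery or for starting other cancer treatments", which is a preference and not a requirement.
- **Definition of T1 (same section).** The second evaluation follows pre-hospitalization in both arms, with a further condition in one: "and post psychological consultation for the experimental group; T1". Between T0 and T1, "the experimental group will meet the psychologist for the consultation and the control group will not receive any intervention". Nothing is said about an experimental dyad that does not meet the psychologist.
- **Exclusion rule (Data analyses).** "If a subject does not complete T1 and T2 he/she will be excluded from the analysis". The same section plans mixed-effects linear models for repeated measures, with the patient as random effect.
- **Which scales depend on T1 (Table 1).** SDM-Q-9, CARE and CPS are marked at T0 and T1 only. HADS, MSPSS and SF-12 are marked at all three times. The ADQ, which carries the sample size, is marked at T2 only, and T2 is counted from the start of medical treatment in both arms.

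**The concern.** Attendance is decided after randomisation and can fail in only one arm. If whether T1 is defined depends on attendance, and being analysed depends on T1, the plan's rules can remove dyads from the experimental arm for a reason that has no counterpart among controls. The consultation asks two people to attend a 60-minute session during the diagnostic period, with T0 and T1 about 4 weeks apart on average, so some non-attendance is realistic.

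Attenders may differ from non-attenders in motivation, cooperation within the dyad or burden of illness. These lie close to what the ADQ, HADS, MSPSS and SDM-Q-9 measure. The estimated group difference would then mix the effect of the consultation with selection, and the protection given by randomisation would be lost for the affected scales. For the ADQ the loss would also be needless, because its collection at T2 does not depend on the consultation.

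**Working it through.** **1. The plan's own figure.** Inputs from Sample size and power calculation: difference 3, SD 5 (d = 3/5 = 0.6), two-sided 5%, power 80%, 1:1 allocation.

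n per arm = 2 × (1.960 + 0.842)² / 0.6² = 43.6, so 44 per arm and 88 in total, as stated. Power at 44 per arm is 80.4% by the normal approximation and 79.5% by the t-test. This figure is not in dispute; it supplies the base for what follows.

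**2. What happens to an experimental dyad that never attends, if no T1 is taken because T1 is defined as post-consultation**

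| Reading of the exclusion rule | ADQ (T2 only) | HADS, MSPSS, SF-12 (T0, T1, T2) | SDM-Q-9, CARE, CPS (T0, T1) |
|---|---|---|---|
| Missing either T1 or T2 excludes | Lost, though obtainable | Lost, though T2 obtainable | Lost |
| Only missing both excludes | Kept | T2 kept | No post-baseline value |

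A control dyad equally unlikely to have attended still has a defined T1. On the second reading the ADQ comparison is not affected, but SDM-Q-9, CARE and CPS are. SDM-Q-9 and CPS bear directly on treatment decision-making, which is part of the primary aim.

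**3. Illustrative size under the first reading.** Two inputs are not in the document and are assumed: q, the share of the experimental arm that does not attend and is excluded (5% to 30%), and G, the mean outcome of would-be attenders minus non-attenders in the absence of any consultation effect (1.25 to 5 points, that is 0.25 to 1.0 SD).

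The control mean is (1 − q) × attenders + q × non-attenders, and the analysed experimental mean is attenders only. So bias = q × G. With SD 5 and 44 × (1 − q) against 44 analysed, the type I error comes from the noncentral t with noncentrality (q × G / 5) / √(1/n₁ + 1/44).

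| q | G (points) | n₁ | Bias (points) | Share of 3 points | Type I error |
|---|---|---|---|---|---|
| 10% | 2.5 | 40 | 0.25 | 8% | 5.6% |
| 20% | 2.5 | 35 | 0.50 | 17% | 7.2% |
| 30% | 2.5 | 31 | 0.75 | 25% | 9.7% |
| 20% | 5.0 | 35 | 1.00 | 33% | 14.1% |
| 30% | 5.0 | 31 | 1.50 | 50% | 24.3% |

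Worked line, q = 20%, G = 2.5: bias = 0.2 × 2.5 = 0.5 points = 0.1 SD; √(1/35 + 1/44) = 0.226; noncentrality = 0.1/0.226 = 0.44; type I error 7.2%. At the low end, q = 5% and G = 1.25 give a bias of 0.06 points and a type I error of 5.0%.

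**4. Power if all are analysed as randomised.** If non-attenders gain nothing, the effect is 0.6 × (1 − q). At 44 per arm, q = 10% gives d = 0.54 and power 70.7%; q = 20% gives d = 0.48 and power 60.5%, against 79.5% with full attendance.

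**The case against.** The strongest reply is that the one-sided loss needs inferences which the text does not force.

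- **T1 for non-attenders.** A reader might infer that T1 is withheld from dyads that miss the session. The protocol does not say so. T1 is also anchored to pre-hospitalization, the T0 survey goes out by electronic link, and Table 1 puts no attendance condition on T1. The parenthesis may only describe the expected sequence. This stands as to certainty. But as worded the visit is post-consultation in that arm, so a non-attender has no visit that meets the definition, and staff must either depart from it or omit the assessment.
- **The exclusion rule.** A reader might infer that anyone without T1 is dropped. Read literally, the rule may remove only those missing both visits, and a non-attender's T2 ADQ would stay in. This stands. On that reading the problem narrows to the scales whose last assessment is T1.
- **Attenders against all controls.** The documents do not support this. The same rule removes control non-completers, and the Discussion expects a possibly large control loss. The contrast is between completers in both arms.
- **Bias in favour of the intervention.** Plausible but not established. Controls who stay may also be selected for motivation, although that is a different process and cannot be assumed to cancel an attendance filter. For scales measured at T0, the baseline term in the model would absorb part of any gap; the illustration ignores this.
- **Arms defined by treatment received.** The phrase "dyads receiving a psychological support consultation (experimental group" could suggest this, but the sentence introducing it speaks of random assignment, and the text that follows refers to assigned dyads. It names the allocated condition.

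It can also be said that an article leaves analysis sets to a fuller document. That would excuse silence. Here the article states an arm-specific visit definition and a post-randomisation exclusion, and it is these two statements together that cause the difficulty.

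**Conclusion.** The point holds in limited form. The T1 definition leaves experimental non-attenders without a defined T1, and the exclusion rule can then remove them, or all their post-baseline data on SDM-Q-9, CARE and CPS, from one arm only. For the ADQ the effect arises only if missing either visit leads to exclusion. The result would be attending completers compared with control completers.

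The document fixes neither the size nor the direction of any bias. Over the assumed ranges it runs from 0.06 to 1.5 points on the 3-point target, with type I error from about 5% to 24%. The middle case (20% non-attendance, 2.5-point gap) gives 0.5 points and about 7%. These figures assume that no T1 is taken from non-attenders, that either missing visit excludes, that controls are not themselves selected, and that SD 5 still applies among attenders. This should be corrected before analysis. It does not show that the trial's result would be wrong.

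**What to change.** In Study design and setting, define T1 in both arms as the assessment after pre-hospitalization, whether or not the consultation took place.

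In Data analyses, replace the exclusion sentence with three statements: all dyads are analysed in the arm to which they were randomised; any available T1 or T2 data are kept, in the planned mixed model for the repeated scales and in the T2 comparison for the ADQ; non-attendance at the consultation is not a reason for exclusion.

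Record attendance (yes/no) for each experimental dyad, and report an attenders-only comparison as supportive at most.

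The cost is a few sentences and one data field. The real downside is dilution: if non-attenders gain nothing, power falls from about 80% to about 71% at 10% non-attendance or about 61% at 20%, with 44 analysed per arm. The team should decide in advance whether the planned 102 dyads leave room for that.
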